### Treatment

All patients receive pre-, peri-, and post-operative care according to the local bariatric protocol. All patients are urged to lose bodyweight before surgery to decrease surgical risks. Patients are not required to undergo a low calorie liquid diet prior to surgery. Thrombosis prophylaxis is administered in the first post-operative week and a proton-pump inhibitor is prescribed for 3 months after surgery. Patients are advised to lifetime use of vitamins. Initial diabetes management after surgery is coordinated by the internist and during the first months after surgery transferred to a patient’s own diabetes team.

### RYGB

A RYGB consists of a gastric pouch with a volume of approximately 25 ml, a 50-cm biliary limb, and a 150-cm alimentary limb. The alimentary limb is brought up antecolic and antegastric and is anastomosed to the gastric pouch with a linear stapler and a running barbed wire. The jejunojejunostomy connects the alimentary and the biliary limb into a common channel. This anastomosis is fully stapled or closed with a running barbed wire [16, 17]. The mesenteric windows are closed with staples. The RYGB is depicted in Fig. 2.

**Fig. 2 Fig2:**
[figure not shown]
Roux-en-Y gastric bypass

### OAGB

The OAGB consists of a long-sleeved and narrow stomach pouch parallel to the lesser curvature, from the Crow’s foot up to the angle of His. The pouch is connected to the jejunum 200 cm distal to the ligament of Treitz. The jejunal loop is brought up antecolic and antegastric and is anastomosed to the pouch to form the gastrojejunostomy with a linear stapler and a running barbed wire. The Peterson-window is closed with staples in patients in the Spaarne Gasthuis [17, 18]. The OAGB is shown in Fig. 3.

**Fig. 3 Fig3:**
[figure not shown]
One-anastomosis gastric bypass

### Outcome measures

The primary outcome measure of the DIABAR-trial is glycemic control, as measured by the difference in Hba1c 12 months after RYGB and OAGB. Glycemic control at 6 months, 2–5 and 10 years of follow-up, and the remission of T2DM at 1–5 and 10 years of follow-up are secondary outcome measures. For remission of diabetes, we will use the proposed definition according to ADA consensus report 2021 primarily (Hba1c < 6.5%), and in a secondary analysis, the more strict cut-off < 5.7% will be used [19]. Other secondary outcome measures are related to the interplay of obesity, NAFLD/NASH, and cardio-vascular performance. Table 1 shows the schedule of enrolment and study procedures (SPIRIT-format). All measurements will be performed by the researchers and physicians according to a standard operating procedure.

*Demographics* consist of age, sex, ethnic background, medical history, use of medication, history of weight-change, intoxications, educational level, employment status, and physical activity. Prior to surgery, patients will be asked about their expectations of metabolic surgery in terms of weight loss.

*Biometric data* consist of weight, height, waist to hip ratio, temperature, bioelectrical impedance (BIA), electrocardiogram (ECG), blood pressure, pulse, stroke volume, cardiac output, and systemic vascular resistance (Nexfin).

*Dutch versions of validated questionnaires* are used for evaluation of psychological measures. This includes quality of life, self-efficacy, hunger and craving, social support, depression, and body image, as previously described in the protocol of the BARIA-study [15]. Food intake is registered using food diaries. Gastro-intestinal complaints are assessed with the gastro-intestinal quality of life (GIQLI) questionnaire [20].

*Peripheral blood* will be drawn at various time points as part of the regular follow-up and includes hemoglobin, leukocytes, C-reactive protein, HbA1c, glucose, c-peptide (only baseline), electrolytes, kidney function, hepatic enzymes, lipid profile, iron, vitamins, and thyroid profile.

*Mixed meal test*, a 2-h oral mixed meal test (MMT), will be performed three times in the course of the study [21]. During the MMT, the patient will consume two 125 ml Nutridrink compact drinks (Nutricia®). At set time points during this test, blood will be obtained through an intravenous line and will be used to measure insulin sensitivity, plasma metabolites, and bile acids.

*Oral swabs and fecal and urine samples* will be collected at various time points. This includes 24-h and morning fecal and urine samples, as well as a gingival swab.

*Ultrasound of the gallbladder* will be performed to detect gallstones prior to and during follow-up after surgery.

*Surgery*: patients will either undergo a RYGB or OAGB according to randomization. During surgery, the following tissue biopsies will be obtained: subcutaneous fat from any of the trocar incisions, tissue from the greater omentum and visceral fat from the omental appendices of the colon transversum, and jejunum at the jejuno-jejunostomy site (only in patients that undergo a RYGB) and liver biopsy (of segment 3 or 5). In selected cases, and only if considered safe by the surgeon, blood will be drawn from the portal vein at the beginning of the surgery.

*Surgical endpoints* are time from incision of the skin to closure of the wound, conversion, hospital stay, readmission, and complications and mortality ≤ 30 days and > 30 days of surgery.

*Re-operation/endoscopys*: in case a patient enrolled from the Spaarne Gasthuis will undergo another, and non-acute, abdominal surgery longer than 30 days after the RYGB or OAGB, the patient will be asked for informed consent to obtain biopsies from liver and fat depots. In case of cholecystectomy, the patient will be asked for consent to collect bile acid and gallbladder tissue. If a patient enrolled from the Spaarne Gasthuis needs to undergo an endoscopy indicated by upper gastro-intestinal complaints, the patient will be asked for permission to obtain a biopsy of the small intestine.

### Data handling and storage

All electronic data will be stored in an electronic case record form, which was designed in the program Castor Electronic Data Capture (Ciwit BV, the Netherlands). This software is compliant with “good clinical practice.” All data will be handled confidentially and will be registered under a unique code in accordance with the Dutch Personal Data Protection Act (Wbp).

Study materials will be stored for a period of 20 years at − 80° Celsius in the DIABAR-biobank. Blood samples and other materials collected during the trial will be subjected to extensive testing, as further elaborated in the study-protocol of the closely related BARIA-study [15]. Briefly, this testing encompasses evaluation of plasma metabolites in peripheral blood samples taken prior to and after the MMT and in portal vein blood; assessment of gut microbiome and metabolites from fecal samples; qPCR of liver, jejunal, and fat tissue biopsies; assessment of intestinal immunological cells in Peyer’s patches, in adipose and liver tissue and in peripheral blood samples; and evaluation of immunological parameters in small intestinal and adipose tissue.

### Statistical analysis

#### Power calculation and sample size

Sample size calculation was performed based on a retrospective analysis of patients after RYGB (*n* = 90) and OAGB (*n* = 37). Patients were matched in a 3:1 ratio on baseline age, BMI, and gender. The mean pre-operative Hba1c in the RYGB group was 7.5 ± 1.4% and 7.5 ± 1.5% in the OAGB group (*p* = 0.97). Null hypothesis is as follows: there is no difference in decrease of Hba1c at 12 months after RYGB or OAGB in patients with T2DM. Alternative hypothesis: the decrease in Hba1c after OAGB is higher than after RYGB in patients with T2DM at 12 months after surgery. For sample size calculation, the mean Hba1c of both groups was compared with a two-sided significance level of *P* < 0.05 and a power of 80%. Based on the retrospective results, 100 subjects per group will be required. Considering a 10% dropout rate, 220 patients are needed.

#### Analysis of endpoints

The statistical analyses will be performed using SPSS statistical software (IBM corporation, New York, USA). Data will be expressed as mean, standard deviation, or median and range, as appropriate. Differences in categorical variables will be evaluated with the chi-square or the Fisher exact test, as appropriate; continuous data will be compared with the Student *t* test or Mann-Whitney *U*. Multivariate analysis and ANOVA for repeated measures will be used. *P*-values < 0.05 will be considered statistically significant. Clinical complications will be evaluated by an independent adjudication committee. An interim analysis will be performed at 60 patients per group. A modified intention to treat analysis will be performed (all randomized patients that initiate treatment in the arm they are allocated to, i.e., exempting those who do not undergo surgery at all) in which “last value carried forward” will be used for missing observations. A per-protocol analysis will be carried out as well to account for effects of revisional surgery (i.e., revision from OAGB to RYGB). For this analysis, only data of patients gathered before revisional surgery will be used.

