**Methods:**

The DIABAR-trial is an open, multi-center, randomized controlled clinical trial with 10 years follow-up which will be performed in 220 severely obese patients, diagnosed with T2DM and treated with glucose-lowering agents. Patients will be randomized in a 1:1 ratio to undergo RYGB or OAGB. The primary outcome is glycemic control at 12 months follow-up. Secondary outcome measures are diverse and include weight loss, surgical complications, psychologic status and quality of life, dietary behavior, gastrointestinal symptoms, repetitive bloodwork to identify changes over time, glucose tolerance and insulin sensitivity as measured by mixed meal tests, remission of T2DM, presence of non-alcoholic fatty liver disease/non-alcoholic steatohepatitis in liver biopsy, oral and fecal microbiome, cardiovascular performance, composition of bile acids, and the tendency to develop gallstones.

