**Discussion:**

The DIABAR-trial is one of the few randomized controlled trials primarily aimed to evaluate the glycemic response after the RYGB and OAGB in severe obese patients diagnosed with T2DM. Secondary aims of the trial are to contribute to a deeper understanding of the mechanisms that drive the remission of T2DM in severe obese patients by identification of microbial, immunological, and metabolic markers for metabolic response and to compare complications and side effects of RYGB and OAGB.

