### Trial status

The first patient was enrolled and randomized on October 23, 2017. The study is ongoing. At the time of writing, 86 patients are enrolled in the Spaarne Gasthuis and 14 in the Franciscus Gasthuis. Recruitment is estimated to be completed in 2024. Current trial protocol is version 8.1, July 2020.

Results of the trial will be presented in a manuscript and offered to a peer-reviewed journal.

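### For complications and deaths after 30 days, the stated rules (chi-square or Fisher, last value carried forward) take no account of incomplete follow-up and would understate absolute late risk

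*Protocol article*

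**What the plan says.** The relevant statements are spread over several sections of the protocol article.

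- **Endpoint.** Outcome measures lists among the surgical endpoints "conversion, hospital stay, readmission, and complications and mortality", split at 30 days: "complications and mortality ≤ 30 days and > 30 days of surgery". The late window has no stated end. Table 1 schedules surgical endpoints at 14 and 42 days, 6 months, and years 1, 2, 3, 4, 5 and 10.
- **Aim.** The Discussion paragraph of the Abstract gives as a secondary aim "to compare complications and side effects of RYGB and OAGB". The main Discussion names internal herniation after RYGB, and biliary reflux and its consequences after OAGB.
- **Test.** Analysis of endpoints says: "Differences in categorical variables will be evaluated with the chi-square or the Fisher exact test, as appropriate". It makes no exception and does not mention complications. It then adds: "Multivariate analysis and ANOVA for repeated measures will be used".
- **Missing data.** The same section applies "last value carried forward" in the modified intention-to-treat analysis, again without exception.
- **Per-protocol analysis.** Data after revisional surgery are dropped; the example given is revision from OAGB to RYGB.
- **Horizon and entry.** The Abstract describes a "randomized controlled clinical trial with 10 years follow-up which will be performed in 220 severely obese patients". Under Trial status the first patient was randomised in October 2017, and "Recruitment is estimated to be completed in 2024".

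The only sentence in Analysis of endpoints that is specific to complications says that an independent committee will adjudicate them.

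**The concern.** Late complications accrue over years, and some patients will stop attending before year 10. A valid estimate of the 5- or 10-year risk must use how long each patient was observed. None of the named methods is stated to do so.

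The problem arises from two rules acting together. Carry-forward turns a last observation of no complication into no complication at every later visit, and the patient stays in the denominator. The chi-square or Fisher test then compares the resulting proportions. The test itself does not decide who counts as event-free; the imputation rule and the denominator do.

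Two things are at stake. The absolute late risks, which patients and surgeons would weigh against glycaemic benefit, come out too low. In addition, if follow-up is shorter in one arm, part of any difference in complications, or of its absence, would reflect observation time.

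**Working it through.** **The plan's own figure.** Power calculation and sample size gives 100 per group and 10% dropout: 2 × 100 × 1.10 = 220, or 110 per arm, which reproduces the stated total. That figure concerns HbA1c at 12 months, and the dropout has no stated time horizon. The article gives no late complication rate and no long-term loss rate, so all event and loss rates below are assumptions.

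**Understatement of absolute risk.** Assume constant hazards of event (h) and of loss (g) over T years, true risk p by T, and a fraction L lost by T:

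- h = −ln(1 − p)/T and g = −ln(1 − L)/T
- crude proportion = h/(h + g) × [1 − exp(−(h + g)T)] = h/(h + g) × [1 − (1 − p)(1 − L)]

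For p = 10% at T = 5 years, hT = 0.1054:

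| Lost by year 5 | gT | h/(h + g) | 1 − (1 − p)(1 − L) | Crude proportion | Relative shortfall |
|---|---|---|---|---|---|
| 10% | 0.1054 | 0.500 | 0.19 | 9.5% | 5% |
| 20% | 0.2231 | 0.321 | 0.28 | 9.0% | 10% |
| 30% | 0.3567 | 0.228 | 0.37 | 8.4% | 16% |
| 40% | 0.5108 | 0.171 | 0.46 | 7.9% | 21% |

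The formula depends only on p and L at the horizon. For a true 10-year risk of 20%, the crude proportion is 19.0%, 16.9% or 14.6% with 10%, 30% or 50% lost by year 10.

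**Comparison between arms.** These results use a 10-year horizon and 110 per arm. Type I error and power come from 4,000 simulated trials per scenario.

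| True risk | Loss | Crude result | Chi-square rejects | Log-rank rejects |
|---|---|---|---|---|
| 20% vs 20% | 30% vs 30% | equal | 0.044 | 0.043 |
| 20% vs 20% | 10% vs 30% | 19.0% vs 16.9% | 0.065 | 0.046 |
| 20% vs 20% | 20% vs 50% | 18.0% vs 14.6% | 0.106 | 0.052 |
| 20% vs 10% | 30% vs 30% | ratio 2.0, difference 8.5 points | 0.50 | 0.50 |
| 20% vs 10% | 30% vs 10% | ratio 1.78 | 0.38 | 0.51 |
| 20% vs 10% | 10% vs 30% | ratio 2.25 | 0.64 | 0.49 |

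With equal loss, the ratio, type I error and power match those of the log-rank analysis; only the absolute risks and their difference shrink (8.5 points instead of 10). With unequal loss, the bias can go in either direction.

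**Sources of unequal follow-up in the document.** Entry from 2017 to 2024 spreads follow-up by up to about 7 years in an analysis made before all patients reach the visit concerned (about 2034 for year 10). Randomisation balances entry time between arms on average, so this mainly affects absolute risks. The per-protocol analysis is different: if revisions occur mainly from OAGB to RYGB, truncation at revision shortens observation in one arm.

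**The case against.** The strongest reply is that the article never says how late complications will be analysed. The chi-square sentence is general, and it suits 30-day events and outcomes at a fixed visit, such as remission. The carry-forward rule is not tied to complications. The article condenses a full protocol (version 8.1), and a time-to-event method for a secondary safety endpoint could well stand there or in an analysis plan.

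Much of this stands. A reader might infer that the plan declares a comparison of crude 10-year proportions with lost patients counted as complication-free. The document does not say that; it is the consequence of applying two general rules as written. The point remains because both rules are stated without exception, and carry-forward is unsuitable for an accruing event.

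A reader might also infer that staggered entry biases every late comparison. It does not: visits are timed from surgery, and an analysis at a visit that all patients could have reached gives equal planned follow-up.

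A third tempting reading is that the safety comparison is distorted in any case. The simulations do not support this. Distortion requires unequal loss or follow-up, and apart from the per-protocol truncation the document gives no reason to expect either.

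Finally, the effect may be small. At 10% loss, the shortfall on a true 10% is 0.5 points, about half a patient in 110. With equal true 5-year risks of 10% and loss of 20% versus 40%, the spurious gap is 9.0% versus 7.9%, about 1.2 patients in 110.

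**Conclusion.** The point holds in a limited form. Applied as written to complications and deaths after 30 days, the stated rules keep patients lost without an event as event-free and understate absolute late risk. The relative shortfall is about 5% with 10% loss and 21% with 40% loss, for an assumed true 5-year risk of 10% with constant hazards and loss unrelated to the event. With equal loss, the absolute difference between arms shrinks in proportion, while the risk ratio and type I error are preserved.

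Bias between arms is conditional on unequal loss or follow-up. The one route visible in the document is the per-protocol truncation at revision, if that analysis is used for complications. Long-term loss is unknown, so the true size cannot be stated. Events within 30 days, where loss should be small, and the 12-month HbA1c endpoint are outside this point. It deserves correction because comparing complications is a declared aim and the better method needs little change.

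**What to change.** In Analysis of endpoints:

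1. Keep chi-square or Fisher for events within 30 days.
2. Exempt complications and mortality after 30 days, and revisional surgery, from last value carried forward.
3. For these endpoints, estimate cumulative incidence by arm with censoring at last contact: Aalen-Johansen with death as a competing event for complications and revision, and Kaplan-Meier for mortality.
4. Report 1-, 5- and 10-year risks by arm with 95% confidence intervals, and compare arms by log-rank test or Cox model.
5. Report revisional surgery as an event in its own right, because stopping observation at revision in the per-protocol analysis may be related to the complications of interest.

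The cost is a change of analysis wording; visits and adjudication are already planned. Event and last-contact dates must be recorded and used, and the 30-day split alone does not guarantee that they are. No visit is scheduled between years 5 and 10, so some event times may be known only to an interval. The methods also assume non-informative censoring, so loss to follow-up should be reported by arm.

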### Informed consent and randomization

Patients are first informed on the study during the preoperative screening program, which consists of consultations with a surgeon, an internist, a dietician, a psychologist, and meetings for patient education. If patients proceed towards surgery, they are screened for inclusion into the study. Patients are asked for written informed consent to participate in the study by the surgeon and also to store study materials in the DIABAR-biobank. After informed consent is obtained by the surgeon at the outpatient clinic, patients will be randomly assigned by the surgeon to undergo a RYGB or OAGB in a 1:1 ratio. Randomization will be performed with the use of electronic block-randomization with the program *Castor Electronic Data Capture* (Ciwit BV, the Netherlands). Block size varies between four and six; there is no stratification. Patients and surgeons are directly informed on the outcome of the randomization.

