The underlying physiological and molecular mechanisms responsible for the antidiabetic effects of metabolic surgery have not been fully understood. Proposed theories include acute reduced caloric intake possibly-in part-responsible for the weight-independent antidiabetic effect occurring directly post-surgery, as well as a middle-to long-term antidiabetic effect of surgery-induced weight loss [50]. Rapidly occurring enhanced glycemic control might also be due to altered anatomy and signaling/sensing of the gastro-intestinal tract, formulated in the foregut and hindgut hypothesis [51, 52]. Among other factors that are recognized to be of potential influence are the immune system, the intestinal microbiome, and altered bile acid metabolism [53–56]. Also, there is an association between obesity, non-alcoholic fatty liver disease (NALFD), and insulin resistance/T2DM, with reports of the presence of (some form of) NAFLD in up to 80% of patients undergoing weight loss surgery [57, 58]. It is likely that not one (dominant) factor or one mechanism is responsible for the beneficial glucoregulatory effects of metabolic surgery but that the effects are due to an interplay of various pathways. The DIABAR-trial grants the unique opportunity to assess extensive data of patients with T2DM and obesity after two different metabolic procedures and to explore driving mechanisms in metabolic response.

A few limitations have to be acknowledged. First, for logistic reasons, patients will not be stratified upon the use of insulin or the duration of T2DM. Second, the authors are aware of and responsible for the extent of the study procedures patients are subjected to. Therefore, the study is performed by a research nurse, who stays in close contact with participating patients and monitors how patients perceive their participation in the study. To meet with the patient’s time investment, patients receive a financial reimbursement. Third, patients are required to lose weight prior to surgery. This might influence the metabolic changes induced by surgery; yet patients in both arms of the study are projected to the same pre-surgical weight loss and it lowers the surgical risk.

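### The primary variable is named inconsistently (12-month HbA1c or its decrease), so the 80% power cannot be tied to the hypothesis, and the only stated test for comparing arms makes no use of baseline HbA1c as a covariate

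*Protocol article*

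**What the plan says.** Three statements in the Protocol article describe what is compared.

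- Outcome measures: the primary outcome is "glycemic control, as measured by the difference in Hba1c 12 months after RYGB and OAGB". This reads as a comparison of 12-month levels.
- Power calculation and sample size, null hypothesis: "there is no difference in decrease of Hba1c at 12 months after RYGB or OAGB in patients with T2DM". The alternative is directional: "the decrease in Hba1c after OAGB is higher than after RYGB in patients with T2DM at 12 months after surgery". Both concern change from baseline.
- Same section, basis of the calculation: "the mean Hba1c of both groups was compared with a two-sided significance level of" 0.05, with 80% power. It does not say whether this is the 12-month level or the change. The only means and SDs printed are pre-operative: 7.5 ± 1.4% (RYGB) and 7.5 ± 1.5% (OAGB).

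On the test, Analysis of endpoints says "continuous data will be compared with the Student" t test or Mann-Whitney U, as a general rule and without covariates. The next sentence adds multivariate analysis and repeated-measures ANOVA, but names no endpoint, covariate or purpose. No single test or model is designated for the primary outcome.

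Table 1 schedules regular laboratory work both at screening and on the day of surgery. The article does not say which value counts as baseline for a decrease.

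**The concern.** The 12-month level and the decrease have different variances, so the same 100 patients per arm give different power for each. A reader cannot tell which of them the 80% describes, and no figure in the article settles it. With two candidate variables and two candidate tests, the primary p-value is not fixed in advance by this text. That matters more in an open trial with a planned interim analysis at 60 per group and no data monitoring committee.

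Precision is also at stake. Baseline HbA1c is part of the regular bloodwork at both current centres. The stated between-arm rule either ignores it (12-month level) or subtracts it in full (decrease). Neither is the most efficient use of a measurement already paid for.

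**Working it through.** **Inputs from the article:** 100 per group, two-sided 0.05, power 80%, 1:1 allocation, pre-operative SDs 1.4 (n = 90) and 1.5 (n = 37). **Not in the article:** the expected difference, the 12-month SD, the SD of change, and the correlation r between baseline and 12-month HbA1c. The values of r below are assumptions, shown as a range.

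**1. Trying to reproduce 100 per group.** This cannot be done forwards, because no difference is given. Solved backwards, the standardised difference is d = (1.960 + 0.842) × √(2/100) = 0.396. On the pooled pre-operative SD, √((89 × 1.4² + 36 × 1.5²)/125) = 1.43, this would be 0.396 × 1.43 = 0.57 HbA1c points, which the article does not state. Other pairs fit equally well: 0.40 with SD 1.0 gives 99 per group, 0.55 with SD 1.4 gives 102, and 0.60 with SD 1.5 gives 99. The figure of 100 therefore does not reveal which variable was sized. The total follows as 200 × 1.10 = 220.

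**2. Relative variances, with equal SDs at baseline and 12 months.** 12-month level: 1. Decrease: 2(1 − r). ANCOVA on baseline: 1 − r². Power = Φ(2.802/√(relative variance) − 1.960) when the 80% belongs to the 12-month level.

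Example at r = 0.3. Decrease: 2.802/√1.4 = 2.368, and Φ(0.408) = 66%. ANCOVA: 2.802/√0.91 = 2.937, and Φ(0.977) = 84%.

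**3. If the 80% belongs to 12-month HbA1c:**

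| r | 12-month level | Decrease | ANCOVA |
|---|---|---|---|
| 0.2 | 80% | 60% | 82% |
| 0.3 | 80% | 66% | 84% |
| 0.4 | 80% | 73% | 86% |
| 0.5 | 80% | 80% | 90% |
| 0.6 | 80% | 88% | 94% |
| 0.7 | 80% | 95% | 98% |

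To one decimal, ANCOVA at r = 0.4 is 86.4%; rounding the inputs gives 86 or 87.

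**4. If the 80% belongs to the decrease:** the decrease has 80% at every r by construction. The detectable difference is then d × √(2(1 − r)), and the other two analyses have:

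| r | 12-month level | ANCOVA |
|---|---|---|
| 0.2 | 94% | 95% |
| 0.3 | 91% | 94% |
| 0.4 | 87% | 92% |
| 0.5 | 80% | 90% |
| 0.6 | 71% | 88% |
| 0.7 | 58% | 86% |

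With equal SDs, level and decrease agree only at r = 0.5. ANCOVA is at least as powerful as either in every row of both tables.

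**5. Sensitivity to unequal SDs.** If HbA1c varies less after surgery, the decrease fares worse under step 3. With a 12-month SD of 0.7 times the baseline SD (assumed), its power is 47, 53 and 60% at r = 0.3, 0.4 and 0.5. It reaches 80% only when r exceeds 1/(2 × 0.7) = 0.71.

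**The case against.** The strongest reply is that this is a condensed article, that a full protocol (version 8.1) exists, and that covariate lists and the choice between t test and Mann-Whitney U commonly sit there or in an analysis plan. That stands for missing detail. It does not remove the disagreement between the outcome section, the hypotheses and the sample size.

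Second, under randomisation the level and the decrease estimate the same treatment difference apart from sign, and an unadjusted test of either is valid. This also stands: the two wordings differ in precision, not in the clinical question.

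Several stronger readings are tempting and are not supported:

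- *That an unadjusted test is the designated primary analysis.* The t test or Mann-Whitney line is a general rule for continuous data, and the sentence after it names further methods. It is the natural reading for the primary comparison, but the article does not say so.
- *That the trial has less than 80% power.* This depends on which variable was sized and on an unstated correlation. An unadjusted comparison of 12-month HbA1c keeps its 80% if that was the plan. The loss shown above is relative to ANCOVA.
- *That chance baseline imbalance passes straight into the estimate.* Taking an SD of 1.45, midway between the two printed, the 95% range of imbalance is ±1.96 × 1.45 × √(2/100) = ±0.40 points. With equal SDs only the fraction r of it carries into a 12-month comparison, about 0.12 to 0.20 points at r = 0.3 to 0.5. The standard error already allows for this.
- *That the article concedes insulin use and diabetes duration are uncontrolled.* It says only that "patients will not be stratified upon the use of insulin or the duration of T2DM", in line with "there is no stratification" in the randomisation section. Not stratifying does not rule out adjustment in the analysis.
- *That centre must be adjusted for because OAGB technique differs.* The article reports that "The Peterson-window is closed with staples in patients in the Spaarne Gasthuis", but links this to no effect on HbA1c.

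**Conclusion.** The point holds in a limited form. The article gives inconsistent descriptions of the primary variable, and the 80% cannot be tied to the hypothesis about the decrease, because neither the difference nor a relevant SD is stated. The only rule for comparing continuous data between arms is unadjusted. The sentence on multivariate analysis and repeated-measures ANOVA is too unspecific to supply a baseline-adjusted primary analysis.

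The size is conditional. If the sizing was on the 12-month level with equal SDs, the decrease could fall as low as about 66% at r = 0.3, while ANCOVA gains roughly 4 to 10 points over the planned 80% at r = 0.3 to 0.5. If the sizing was on the decrease, there is no shortfall for the decrease, and ANCOVA still gains. The contradiction is certain from the text; the power figures illustrate what it could mean and do not demonstrate a loss. This should be corrected, but it does not invalidate the trial.

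**What to change.** 1. Make 12-month HbA1c the single primary variable, analysed by ANCOVA with baseline HbA1c as covariate and reported as an adjusted difference with a 95% CI.
2. Define baseline as one named pre-operative value, since HbA1c may be available from both screening and the day of surgery.
3. Restate the null and alternative hypotheses in those terms, two-sided, to match the significance level.
4. State the difference and SD behind 100 per group, and which variable the 80% refers to.
5. Keep the t test or Mann-Whitney U as a sensitivity analysis. Adjustment for centre or insulin use is optional; if wanted, name it now.

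The cost is a dated amendment; no new data or patients are needed. It should be made before outcome data are compared by arm, and so before the interim analysis at 60 per group. The article reports 86 + 14 = 100 patients enrolled at the two current centres but does not say whether any comparison by arm has been made. If one has, the amendment should say so.
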